## Abstract

Cardiovascular disease (CVD) is the leading cause of death worldwide. Physical activity interventions improve almost all modifiable CVD risk factors, but the effect of physical activity on low density lipoprotein cholesterol (LDL‐C) is uncertain. This may be due to lack of research on the feeding status in which the physical activity is performed. The aim of this study is to investigate the effect of fasted versus fed exercise on LDL‐C concentrations in males and females. One hundred healthy participants, equal males and females, aged between 25 and 60 years will be recruited and will undergo a home‐based 12‐week exercise intervention. After baseline testing, participants will be randomized to a fasted exercise (exercise after an 8‐h fast) or fed exercise (exercise 90–180 min after ingestion of 1 g kg^−1^ CHO) group and will perform 50 min of moderate intensity exercise (e.g., 95% heart rate of lactate threshold 1) three times a week either before or after a high carbohydrate (1 g kg^−1^) meal. Participants will visit the laboratory again at week 4 and week 12 and measurements will be taken for body composition, resting blood pressure, fasting blood glucose, lipid profiles and systemic inflammation, lactate threshold, and 14‐day blood glucose control.

## INTRODUCTION

1

Cardiovascular disease (CVD) is the leading cause of death worldwide and accounts for 27% of all deaths in the UK (British Heart Foundation, 2020). It is well established that hyperlipidaemia is associated with an increased risk of CVD, with elevated non‐high density lipoprotein cholesterol (non‐HDL‐C) having the highest attributable risk for CVD in high‐income countries relative to other modifiable risk factors (Yusuf et al., 2020). Moreover, it has been consistently shown that lowering low density lipoprotein cholesterol (LDL‐C) concentrations proportionately lowers CVD events across the entire range of LDL‐C concentrations (Ference et al., 2017).

Physical activity is an attractive strategy to reduce population CVD risk, with clear evidence that becoming more active improves almost all CVD risk factors, such as insulin sensitivity, waist circumference, aerobic fitness, blood pressure and HDL‐C concentrations, and shows an inverse linear relationship with all‐cause and CVD‐related mortality (Blair et al., 1995; Dela et al., 1992; Fagard, 2001; Kokkinos et al., 1995; McDonough et al., 1970). It is, therefore, a notable exception that LDL‐C concentrations exhibit a far less consistent response to changes in physical activity than all other CVD risk factors (Hespanhol Junior et al., 2015; Wewege et al., 2018).

The feeding status in which physical activity is performed has a profound effect on metabolism, which may affect the ability of physical activity to lower LDL‐C concentrations. Carbohydrate intake before and/or during exercise supresses fat oxidation during exercise partly via insulin‐mediated inhibition of net adipose and intramuscular lipolysis, increased re‐esterification rates, and thus reductions in non‐esterified fatty acid (NEFA) availability (Coyle et al., 2001; Enevoldsen et al., 2004; Frayn et al., 2012). Since high lipid turnover in adipocytes is linked to a lower atherogenic lipoprotein profile (Frayn et al., 2012), the reduction in fat oxidation, and thus lipid turnover, during exercise following meal ingestion may explain the inconsistent findings on the effect of exercise on LDL‐C concentrations.

LDL‐C is produced as very low density lipoprotein (VLDL) particles become lipid depleted following hydrolysis by lipoprotein lipase (LPL; Jackson et al., 1976), leading to formation of small dense LDL‐C particles that have a low affinity for LDL receptors (Packard et al., 2000). An acute bout of fasted exercise results in changes in VLDL‐triacylglycerol (TAG) flux compared to fed exercise (Sondergaard et al., 2011), suggesting that reduction in VLDL‐TAG concentrations results from reduced hepatic production or increased skeletal uptake by lipoprotein lipase. Furthermore, a reduction of intramuscular triglyceride (IMTG) as a result of an acute bout of fasted exercise (Edinburgh et al., 2020) could increase LPL activity to replenish IMTG stores (Hardman, 1998). An acute bout of fasted exercise that reduces VLDL‐TAG performed regularly with exercise training may lower VLDL exposure over time, by either reduced hepatic VLDL production or increased LPL activity, thus reducing LDL‐C concentrations.

Biological sex is an important variable in metabolic responses, and thus responses to exercise and feeding should be considered within the context of potential sex differences. It has previously been shown that there are defined differences in lipoprotein metabolism between human males and females (Palmisano et al., 2018) due to endogenous oestrogens, which may influence disease risk of diabetes and CVD. During exercise in a fasted‐state, females can oxidise more fatty acids (FA) per kg of fat‐free mass compared to males exercising at the same relative intensity (Chrzanowski‐Smith et al., 2021). This higher utilisation of FA during exercise in females is due to upregulation of metabolic pathways related to NEFA and TAG uptake, storage and degradation in skeletal muscle (Horton et al., 2002; Lundsgaard & Kiens, 2014). During exercise in the fed‐state, however, it remains unknown whether males and females differ in the suppression of fat oxidation. Given the potential of fat oxidation to reduce atherogenic lipoprotein profiles, the greater fat oxidation in females during fasted exercise could enhance the effect of exercise in a fasted‐state on LDL‐C concentrations.

Our preliminary research (*n* = 30) indicated that exercise performed in the morning before breakfast significantly increased whole‐body lipid oxidation during an acute bout of exercise, and this effect persisted throughout 6 weeks of exercise training sessions (Edinburgh et al., 2020). The group exercising before breakfast (*n* = 9) exhibited a significant reduction in LDL‐C concentrations of 0.41 mmol l^−1^ at the end of the study compared to baseline, providing a similar reduction in LDL‐C concentrations to non‐statin drug therapies (Silverman et al., 2016). In contrast, the group who performed exercise after breakfast saw no change in their LDL‐C concentrations, suggesting feeding status at time of exercise may unlock the ability of exercise to improve LDL‐C concentrations. However, no study to date has directly assessed whether meal timing in relation to exercise alters LDL‐C concentrations following training. Furthermore, it is yet to be assessed if these changes occur in a home‐based training programme over a longer period of time and if biological sex influences the response of meal timing. Therefore, the primary aim of this randomized, parallel study is to assess the effect of physical activity performed before or after a meal on plasma LDL‐C concentrations in males and females. The secondary aim is to assess the effect of physical activity performed before or after a meal on other CVD risk factors. In our preliminary research a difference in response to an oral glucose tolerance test was also observed between the two groups but glucose control over the study period was not assessed. In addition, given that the gut microbiome has been shown to influence exercise adaptations (Mailing et al., 2019), we will explore changes in microbiome species enrichment.

## METHODS

2

### Study design

2.1

This study was approved by Bristol Research and Ethics Committee (22/SW/0061) and registered on ClinicalTrials.gov (ID NCT05279014). The study design will be a randomized, parallel study of 100 inactive males (*n* = 50) and females (*n* = 50) conducted over a 2‐year period (Figure 1). The intervention will be a 12‐week exercise programme in which participants will be randomized to exercise either in a fasted state (FASTED‐EX) or in a fed state (FED‐EX). Participants in the FASTED‐EX group will perform exercise sessions at least 8 h after the last meal to ensure they are in a fasted state (Ruge et al., 2009) and eat a carbohydrate‐based meal after exercise. Participants in the FED‐EX group will perform the exercise sessions 90–180 min after the carbohydrate‐based meal. The sessions will be completed in either the morning or the evening and participants will be stratified for randomisation based on their preference of exercise timing. The participants will attend the physiology laboratory at the University of Bath on three occasions, at baseline, week 4 and upon completion of the intervention (i.e., week 12). The study will be conducted in accordance with the *Declaration of Helsinki* (Figure 1).

**FIGURE 1 eph13326-fig-0001:**
[figure not shown]
Schematic representation of study design. BP, blood pressure; DEXA, dual‐energy X‐ray absorptiometry; SAD, sagittal abdominal diameter.

### Recruitment

2.2

Participants will be recruited by advertisement on the University of Bath website and via posters and adverts throughout the campus (e.g., digital advertisement platforms, university notice boards). Posters will also be placed throughout the local community such as in libraries, community centres and health centres (e.g., GP practices, pharmacies and dentists). The study will also be advertised via email bulletin to the University of Bath students and staff and via social media (e.g., Twitter, Instagram and Facebook). Individuals interested in participating in the study will be asked to contact the principal investigator and will be provided with a participant information sheet. Potential participants will be invited to the university for initial screening and will provide written informed consent prior to commencing study procedures.

### Randomization

2.3

Participants will be randomly allocated into two groups (FASTED‐EX or FED‐EX) using online randomisation software (www.randomization.com) with a 1:1 allocation ratio. Stratification factors will be high (30–40 kg m^−2^) or low (20–29.9 kg m^−2^) body mass index and preference of morning or afternoon exercise.

### Participants and eligibility criteria

2.4

Participants recruited will be between the age of 25 and 60 years old, have a body mass index between 20 and 40 kg m^−2^ and be self‐reported physically inactive (exercise for less than 150 min per week). Female participants will be self‐reported premenopausal. The body mass index was based on representing the general population, whilst a physically inactive criterion was chosen to reflect individuals who are at somewhat of an increased risk of CVD. Individuals who self‐report a diagnosis of diabetes or CVD, take any medication that could pose undue personal risk or introduce bias into the study such as statins for lipid disorders, or have cardiovascular contraindications to exercise testing will be excluded. Individuals with weight instability (>3 kg change in body mass over last 6 months) or females who are pregnant or lactating will be excluded.

### Outcome measures

2.5

An intention‐to‐treat analysis will be reported for all outcome measures. The primary outcome measure will be change in fasting plasma LDL‐C concentrations at week 12. Secondary outcomes include change in fasting LDL‐C concentrations at week 4, and change in fasting plasma HDL‐C concentrations, fasting plasma VLDL‐rich triglyceride concentrations, fasting plasma total cholesterol concentrations, fasting plasma apolipoprotein B concentrations, apolipoprotein B/apoliporotein A ratio, fasting plasma triglyceride concentrations, plasma C‐reactive protein concentrations, fasting plasma glucose concentrations, fasting plasma insulin concentrations and fasting plasma NEFA concentrations at week 4 and 12. Tertiary outcomes measures include change in body mass, waist to hip ratio, fat mass, fat‐free mass, sagittal abdominal diameter, and systolic and diastolic blood pressure at week 4 and 12, as well as change in gut microbiome species enrichment at week 12 and 14‐day blood glucose control at week 11 and 12. Secondary outcomes are subject to funding.

### Laboratory assessments

2.6

Laboratory assessments will remain the same during all three trial days. Participants will arrive at the laboratory after an overnight fast and 24 h after any strenuous exercise and 48 h after exercise for the last visit. Participants will complete a food diary for 24 h prior to attending the laboratory and replicate this for the subsequent visits. The initial laboratory visit for eumenorrhoeic females will be performed at any stage during the menstrual cycle and due to the study protocol, follow‐up visits will be performed during the same stage, presuming a 28‐day cycle. During laboratory visits, blood pressure and body composition will be measured, followed by a blood sample and  submaximal exercise test.

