#### Exercise intervention

2.6.7

Following baseline testing, participants will undertake a 12‐week home based exercise intervention. Participants will perform 50 min of moderate intensity exercise, 3 days per week, as per current UK physical activity guidelines (Davies et al., 2019). The participant will be able to decide where to complete the exercise sessions. The exercise will be at a low‐to‐moderate intensity (e.g., 95% heart rate of LT1) to ensure greatest fat oxidation in the fasted group (Achten & Jeukendrup, 2004) and will likely represent a brisk walk for most participants. The exercise can be done either outside or on an indoor treadmill. The exercise sessions can be completed on any day of the week but participants will be asked to take at least one rest day between sessions. Participants will be asked to perform at least two out of three of the weekly sessions at the time of day stated during randomisation. The exercise intensity will be prescribed based on heart rate and will equate to 95% of LT1 heart rate. Participants will be provided with a Wahoo activity monitor (Wahoo Fitness LLC, Atlanta, Georgia) and will be asked to monitor their heart rate on the phone application during the exercise sessions. The FASTED‐EX group will perform the exercise after an 8 h fast and will ingest a high carbohydrate meal (1 g kg^−1^ body weight) after each session. The FED‐EX group will exercise 90–180 min after the same high carbohydrate meal. Participants will be able to choose the meal from a predetermined list with prescribed portion sizes ensuring the meal is similar to food they would habitually eat. The meal list includes, but is not limited to, a bowl of cereal and semi‐skimmed milk, toast with jam, bagel and low fat cream cheese, and beans on toast. Participants will be emailed every 2 weeks with their energy expenditure and heart rate during the exercise sessions to encourage compliance with the study protocol. If the intensity of exercise in which LT1 is achieved changes from week 1 to week 4, the prescribed heart rate of the exercise sessions will be amended to ensure the same relative intensity of exercise is undertaken throughout the remaining study period.

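### The pre-visit exercise rule is looser at week 4 than at week 12, so the week-4 secondary contrasts can include an acute, arm-specific effect of a recent session

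*Protocol article*

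**What the plan says.** Participants attend "on three occasions, at baseline, week 4 and upon completion of the intervention (i.e., week 12"). Section 2.6 opens with "Laboratory assessments will remain the same during all three trial days". Its next sentence asks for an overnight fast and for arrival "24 h after any strenuous exercise and 48 h after exercise for the last visit".

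On the study sessions, section 2.6.7 says "The exercise will be at a low‐to‐moderate intensity (e.g., 95% heart rate of LT1") and that this "will likely represent a brisk walk for most participants". On their timing it says "The exercise sessions can be completed on any day of the week but participants will be asked to take at least one rest day between" one and the next. Section 2.1 allows morning or evening sessions.

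The Introduction gives the biological background: "An acute bout of fasted exercise results in changes in" VLDL-triacylglycerol flux relative to fed exercise. It adds that depletion of intramuscular triglyceride after a fasted bout could raise lipoprotein lipase activity.

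Section 2.5 makes week-12 LDL-C the primary outcome. The secondary outcomes are week-4 LDL-C and ten further blood measures at weeks 4 and 12. Section 2.7 compares the arms at each of the two visits by ANCOVA.

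**The concern.** Two things change between week 4 and week 12: the length of the abstention (24 h, then 48 h) and the exercise it covers (strenuous only, then exercise without qualification). A brisk walk below the first lactate threshold is not strenuous on a plain reading, so the rule in force at week 4 may not cover the trial's own sessions at all.

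Randomisation does not remove the difficulty. Both arms follow the same rule, but the last session before the sample is itself fasted in one arm and fed in the other. If a single fasted bout has a short-lived effect that a fed bout lacks, part of a week-4 difference between arms could come from the last session and not from four weeks of training. The 48 h rule limits this at week 12. A reader who sets the two visits side by side to judge the time course would then be comparing results taken under different washouts.

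**Working it through.** The plan states no figure for this point, so the check is a comparison of sections with some counting. The sample-size statement (section 2.8) is consistent on its own inputs: d = 0.82 with 40 per arm gives 95.2% power by the exact t-test, and 80 / (1 − 0.20) = 100. It does not enter the argument.

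**1. Minimum gap from last study session to blood sample**

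| Visit | Sessions counted as strenuous | Sessions not counted as strenuous |
|---|---|---|
| Week 4 | 24 h | none stated |
| Week 12 | 48 h | 48 h |

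On either reading week 4 has the shorter washout. On the second, an evening session followed by a fasted sample the next morning is allowed.

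**2. Whether scheduling closes the gap.** Three sessions a week, each separated by a rest day, repeated weekly, give spacings of 2 + 2 + 3 = 7 days (for example days 1, 3 and 5). The spacing rule applies between sessions, and nothing in it refers to visits. As an illustration, assume that the visit falls on any day of that week with equal chance and that any session on the visit day follows the sample:
- last session on the previous day (visit on day 2, 4 or 6): 3 of 7 days, so less than 48 h;
- last session two days earlier (visit on day 3, 5 or 7): 3 of 7 days, so around 48 h depending on the hour;
- last session three days earlier (visit on day 1): 1 of 7 days, so more than 48 h.

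A gap below 48 h would therefore not be unusual if visits were booked without regard to sessions. How they are actually booked is not stated.

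**3. Outcomes in scope.** Secondary blood contrasts: week-4 LDL-C (1) + 10 measures × 2 visits (20) = 21. At week 4: 1 + 10 = 11.

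**4. Which of the 11 the document links to an acute effect.** The Introduction's mechanism concerns VLDL-triacylglycerol flux, intramuscular triglyceride and lipoprotein lipase. That points chiefly to triglyceride-related and metabolic measures: triglyceride, VLDL-rich triglyceride and NEFA. The Introduction describes no acute fasted-versus-fed effect on HDL-C, total cholesterol, apolipoprotein B or C-reactive protein. For LDL-C it argues from repeated bouts over time, not from a single one.

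**The case against.** The case for leaving the text alone has several parts.

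- **The primary endpoint is protected.** Week-12 LDL-C carries the stricter rule. This stands in full. A reader might infer that the main result is compromised, but the document gives no ground for that.
- **The arms are treated alike.** Both follow the same rule at each visit, so there is no unequal washout by arm. This stands: what is open is whether a week-4 difference is acute or chronic, not whether the randomised comparison is fair.
- **No analysis joins the visits.** A reader might infer that weeks 4 and 12 are to be modelled together or tested against each other. Section 2.7 names only ANCOVA between groups at those weeks. The like-for-like problem therefore concerns interpretation.
- **A recent session is allowed, not required.** This stands. Section 2.6 also asks participants to repeat their 24 h pre-visit food diary, and a session inside that window brings a prescribed carbohydrate meal. That works against a session just before the visit but does not rule one out, because meals are chosen to resemble habitual food.
- **The statement that assessments stay the same may describe only the measurements made on the day.** That is a fair reading, so the point does not rest on a contradiction between the two sentences.
- **Visit instructions may say more.** An article condenses the full protocol, which may define strenuous. But the two intervals are stated here and differ even if study sessions count as strenuous.

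**Conclusion.** The point holds as a limited one. The stated rules allow a study session closer to the week-4 sample than to the week-12 sample, and the document's own rationale gives a reason why such a session could act differently in the two arms. The week-4 contrasts can therefore mix an acute effect with adaptation. The claim that they do mix them would go further than the text.

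The scope is secondary outcomes only: 11 contrasts at week 4, with the concern chiefly on the triglyceride-related and metabolic measures. The size is unknown and may be zero. A reader might try to size it by assuming an LDL-C carry-over and setting it against the planned difference of 0.41 − 0.01 = 0.40 mmol/l. The document reports an acute effect on flux, not on LDL-C concentration, so nothing in it supports such a percentage. Nor can arm-specific carry-over arise at baseline, which precedes randomisation.

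The conclusion assumes that low-to-moderate walking is not barred by a rule on strenuous exercise, or, if it is, that 24 h and 48 h are not equivalent for these measures.

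**What to change.** Apply the last-visit interval to week 4 as well: 48 h since any exercise, with study sessions named explicitly. Using it at baseline too would be preferable for consistency, though arm-specific carry-over does not require it there. Record the time from last session to blood draw at each visit.

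Where week-4 samples have already been taken and session times can be recovered, add a sensitivity analysis restricted to samples that meet the 48 h interval. The heart-rate monitor and phone application may supply those times, but the article does not say that they are stored. Such an analysis selects on behaviour after randomisation and uses fewer participants, so it supports the main week-4 analysis and does not replace it.

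The cost is a line in the visit instructions, one recorded time per visit, and booking the week-4 visit around the three weekly sessions. With spacings of 2, 2 and 3 days, a morning visit at the end of the 3-day spacing, before the next session, gives more than 48 h without dropping a session.

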#### Body composition

2.6.1

Height will be measured using a stadiometer (Seca Ltd, Birmingham, UK) with participants barefoot in the Frankfurt plane. Body mass will be measured using digital scales (Tanita, Amsterdam, The Netherlands) with participants barefoot wearing light clothing. Waist and hip circumference will be measured to the nearest 0.1 cm using a non‐elasticated anthropometric tape (Seca, Hamburg, Germany). Waist circumference will be measured at the mid‐way point between the 12th rib and iliac crest. Hip circumference will be measured at the widest point of the buttocks. Sagittal abdominal diameter will be measured at end‐tidal volume with participants lying supine with their hips and knees flexed at 45° using an abdominal calliper (Holtain Ltd, Crymych, UK). A DEXA scan (Hologic, Marlborough, MA, USA) will be performed to determine fat mass and fat free mass. Participants will be positioned in the centre of the table with feet evenly spaced apart and the arms prone.

